## 4 STUDY GOALS AND OBJECTIVES

This study aims at evaluating the biocompatibility and performance of high permeability polysulfone or polyethersulfone membranes of different surfaces (2.1m^2, 2.2m^2 and 2.7m^2) as well as a vitamin E-grafted polysulfone membrane.

The extraction performances will be evaluated according to the type of techniques: hemodialysis or post-dilution haemodiafiltration.

The evaluation of biocompatibility will allow to assess the potential anti-inflammatory action of each membrane.

This study will be conducted in accordance with the ethical standards of the institutional and/or national research committee and with the 1964 Helsinki declaration and its later amendments or comparable ethical standards.

#### 4.1 Primary objective

- Evaluation of middle molecule ( $\beta 2$  microglobulin, 11.8 kDa) extraction

⇒ **Primary outcome measure**

$\beta 2$  microglobulin reduction ratio

#### 4.2 Secondary objectives

- Evaluation of other middle or large molecule extraction: myoglobin (17kDa), Beta Trace (21kDa), Free immunoglobulin light chains Kappa (23kDa), myostatin (40kDa), glycoprotein orosomucoid (44kDa)
- Extraction of uremic toxins: urea, creatinin, inorganic phosphates (PO4)
- Evaluation of dialysis adequacy (Kt/V)
- Biocompatibility assessment: TNF- $\alpha$  and IL-6 (T0 et Tend)
- Monitoring of nutrition status:
  - 1) quantification of albumin losses during the session in the used dialysate:

A comparative quantification of perdialytic albumin losses using either a " pull/push " syringe allowing to collect continuous spent sampling of dialysate (namely partial dialysate collection, "PDC") or the total dialysate collection (namely "TDC"), which represents the gold standard method to evaluate mass balances achieved during dialysis for a given solute, will be performed in a subgroup of patients (i.e. only 1 center), all being dialyzed with post-dilution HDF (n=8 patients for PDC and n=4 for TDC due to the cumbersome method).
  - 2) dosage of serum albumin and transthyretin before the session
- Inflammation: CRP

## 5 PATIENTS

#### 5.1 Inclusion criteria

- ❑ Adult patient with chronic kidney disease dialyzed for at least one month and treated with the modality used in the center (HD or HDF) for the study
- ❑ Regarding post-dilution HDF mode, patient treated with a minimum convective volume of 20L (cf EuDIAL guidelines)
- ❑ Patient treated with high permeability membrane, with high surface area dialyzer  $\geq 1,8 \text{ m}^2$
- ❑ Patient with vascular access allowing a blood flow rate with a minimum of 300 mL/min
- ❑ Patient covered by the social French health organism
- ❑ Patient informed of the study goals and having signed the informed consent

#### 5.2 Non inclusion criteria

- ❑ Patient with a vascular access not allowing a blood flow rate minimum of 300 mL/min
- ❑ Patient with a fast progressive chronic disease
- ❑ Patient with uncontrolled anemia
- ❑ Patient refusing to sign the informed consent
- ❑ Pregnant or nursing patient
- ❑ Pediatric patient
- ❑ Patient under tutorship

### 5.3 Exit criteria

- ❑ Express request of the patient
- ❑ Medical decision
- ❑ Move to another dialysis center not participating in the study
- ❑ Transplantation
- ❑ Medication without prior agreement of the physician
- ❑ Death

### 5.4 Description of the definitive or temporary shutdown rules

The Health Authorities or the Sponsor may make the decision of a definitive or temporary stoppage of the research.

The Sponsor reserves the right to discontinue the trial if it considers that its continuation is no longer justifiable for medical or methodological reasons.

### 5.5 Management arrangements after the study

Patients will be dialysing under the usual conditions, required by their condition at the end of the research or in case of premature discontinuation of treatment or exclusion of the research. They will no longer be subject to specific reviews relating to research.

## 6 DEVICES

All medical devices are CE marked Class IIb hemodialyzers used in their indications.

All the characteristics, contra-indications and instructions for use are indicated in the instructions for use and these products must be used while respecting them.

- **VIE A**

|                             |                                                      |
|-----------------------------|------------------------------------------------------|
| Dialyzer                    | VIE 21A                                              |
| Membrane                    | VltabranE, Vitamin E-grafted polysulfon Asahi |
| Surface                     | 2,1m^2                              |
| Ultrafiltration coefficient | 89 ml/hxmmHg                                  |
| Dimension of fibers         | Thickness = 45 µm ; inner diameter = 185 µm          |
| Sterilisation mode          | Gamma rays in a humid environment                    |

The Vitamine E-grafted polysulfone membrane, VltabranE™ (VIE) received 6 authorizations for biomedical research:

- Record N° Afssaps : 2006-A00187-44, H-D-vie-mrs  
Coordinator : Pr [name], ATUP Marseille, FRANCE
- Record N° Afssaps : 2006-A00436-45, H-D-ViE  
Coordinator : Pr [name], CHU Montpellier, multicenter study
- Record N° Afssaps : 2008-A00460-55, VIE-AGE  
Coordinator : Pr [name], CHU REIMS, Association ARPDD REIMS
- Record N° Afssaps : 2010-A00638-31, VIE-AP HP-2010  
Coordinator : [name] [name], Bicêtre Hospital
- Record N° ANSM : 2012-A01502-41 ; EVIA 2012  
Coordinator : [name], CHU Montpellier

- Record N° ANSM : 2015-A01391-48 ; EVA.D 2015  
Coordinator : [name], Bordeaux Nord Clinic

And one authorization for routine care research:

- Record N° Afssaps : 2011-A00303-38, VIE AURAD  
Coordinator : Docteur [name], Association AURAD Aquitaine

- LEOCEED 21HX**

|                             |                                             |
|-----------------------------|---------------------------------------------|
| Dialyzer                    | Leoceed 21HX                                |
| Membrane                    | Polysulfone Asahi™                   |
| Surface                     | 2,1 m^2                    |
| Ultrafiltration coefficient | 94 ml/hxmmHg                         |
| Dimension of fibers         | Thickness = 35 µm ; inner diameter = 200 µm |
| Sterilisation mode          | Gamma rays in a dry environment             |

- REXSYS 27H**

|                             |                                             |
|-----------------------------|---------------------------------------------|
| Dialyzer                    | Rexsys 27H                                  |
| Membrane                    | Polyethersulfone                     |
| Surface                     | 2,7 m^2                    |
| Ultrafiltration coefficient | 124 ml/hxmmHg                        |
| Dimension of fibers         | Thickness = 30 µm ; inner diameter = 200 µm |
| Sterilisation mode          | Gamma rays in a dry environment             |

- POLYPURE 22S+**

|                             |                                             |
|-----------------------------|---------------------------------------------|
| Dialyzer                    | Polypure 22S+                               |
| Membrane                    | Polysulfone                          |
| Surface                     | 2,2 m^2                    |
| Ultrafiltration coefficient | 74 ml/hxmmHg                         |
| Dimension of fibers         | Thickness = 40 µm ; inner diameter = 200 µm |
| Sterilisation mode          | Steam                                       |

## 7 METHODOLOGY

### 7.1 Study design, dialyzers and dialysis conditions

This study is a prospective multicenter randomized comparative cross-over trial.

Four different dialysis facilities (AURA Paris, Yvetot clinic, AIDER clinic and Toulouse university hospital center) will be involved in the study.

Eligible patients will be assigned to receive either post-dilution HDF (first two centers) or conventional high-flux HD (last two centers) for 4 weeks. During this period, all patients will be sequentially dialyzed with 4 different dialyzers (one/week, the two first sessions of the week; the

last session of the week being performed with the patient's own dialyzer and used as a wash out session): Leoced 21HX, Polypure 22S+, Rexsys 27H and VIE-21A.

The sequence of dialyzers use will be randomly assigned: per center, device × week allocation scheme will be generated by random permutation of a block of 4 (computer generation). All patients in a given center will follow the scheme allocated to this center. The randomization sequence will be centralized and computed by the statistician.

No run-in period before entering in the active study phase will be performed

Dialysis sessions will be conducted according to usual procedures of the center, with increased monitoring and control of the patients treated with the tested hemodialyzers.

Patients will be treated in HD or post-dilution HDF, according to the usual conditions, specific to each patient. The frequency of dialysis (3 sessions per week), the duration of dialysis (3- 4h), the blood flow of the extracorporeal blood circuit ( $\geq 300$  mL/min), the type (dialysate bicarbonate or other) and the dialysate flow (700 mL/min) will remain unchanged or will be documented in case of modification.

In case of need for adjustment, or changes in prescription of the medication, these changes will be documented. The modifications will respect recommendations.

[figure not shown]

## 7.2 Duration of the study

Duration of the study: 4 weeks.

Period of recruitment: 6 months.

Inclusion start period: November 2016.

### 7.3 Information and consent procedures

Participation in the study will be offered to all 5D CKD patients followed for their extra-renal replacement therapy in one of the 4 investigation centers.

Within each center, after analyzing the medical records of all the patients, each investigator will propose to the eligible patients (compliance with the inclusion and non-inclusion criteria) to participate in the clinical trial by informing them of the completeness of the clinical trial.

An information letter will be given to the patient and commented with the investigator nephrologist. In the event of a favorable response, a visit will be scheduled to sign the consent (cf. Appendix 1) and start the study.

### 7.4 Samples

Blood samples needed for the study will be drawn weekly (for a total of 4 weeks) during the midweek session from the arterial line of the extracorporeal circuit without additional puncture before and after dialysis.

Each withdrawal will include:

#### Tubes needed for local analyses

##### **Before dialysis**

| Type of tube       | Volume | Parameters                   |
|--------------------|--------|------------------------------|
| 1 EDTA tube        | 2,5 mL | Blood count                  |
| 1 heparinized tube | 2,5 mL | Urea, Creatinine, Phosphates |

##### **After dialysis**

| Type of tube       | Volume | Parameters                   |
|--------------------|--------|------------------------------|
| 1 EDTA tube        | 2,5 mL | Blood count                  |
| 1 heparinized tube | 2,5 mL | Urea, Creatinine, Phosphates |

#### Tubes needed for centralized analyses at the CHU of Montpellier

The following tubes will be centrifuged, and serum and plasma aliquoted, frozen and further analyzed in the central laboratory.

### Before dialysis

| Type de tube          | Volume | Parameters              | Nb of aliquots | Volume of serum/plasma |
|-----------------------|--------|-------------------------|----------------|------------------------|
| 1 heparinized tube    | 5 ml   | CRP                     | 1              | 500 µl                 |
|                       |        | Myoglobin               |                |                        |
|                       |        | Beta trace              | 1              | 500 µl                 |
| 1 dry tube            | 7 ml   | Orosomucoid             | 1              | 500 µl                 |
|                       |        | Albumin                 |                |                        |
|                       |        | Transthyretin           |                |                        |
|                       |        | Beta2 microglobulin     |                |                        |
|                       |        | Free light chains kappa | 1              | 500 µl                 |
|                       |        | C3a                     | 1              | 150 µl                 |
|                       |        | C5a                     |                |                        |
|                       |        | TNF-α                   | 1              | 500 µl                 |
|                       |        | IL-6                    |                |                        |
|                       |        | Myostatine              | 1              | 150 µl                 |
| TOTAL before dialysis |        | 12 ml                   |                |                        |

### After dialysis

| Type de tube         | Volume | Parameters              | Nb of aliquots | Volume of serum/plasma |
|----------------------|--------|-------------------------|----------------|------------------------|
| 1 heparinized tube   | 5 ml   | CRP                     | 1              | 500 µl                 |
|                      |        | Myoglobin               |                |                        |
|                      |        | Beta trace              | 1              | 500 µl                 |
| 1 dry tube           | 7 ml   | Orosomucoid             | 1              | 500 µl                 |
|                      |        | Beta2 microglobulin     |                |                        |
|                      |        | Free light chains kappa | 1              | 500 µl                 |
|                      |        | C3a                     | 1              | 150 µl                 |
|                      |        | C5a                     |                |                        |
|                      |        | TNF-α                   | 1              | 500 µl                 |
|                      |        | IL-6                    |                |                        |
|                      |        | Myostatin               | 1              | 150 µl                 |
| TOTAL after dialysis |        | 12 ml                   |                |                        |

## 7.5 Follow-up of the study

A Case Report Form (CRF) will be completed for each patient included in the study. This document contains different sheets: Eligibility Criteria, Patient History, and, for each visit, a Data Collection sheet.

### 7.5.1 Eligibility criteria

The inclusion and exclusion criteria are to be fulfilled by the Investigator.

### 7.5.2 History of the patient

Items to collect are as follows:

- Patient data: gender / age / date of start dialysis / dry weight
- Characteristics of dialysis session: number of sessions per week / name of the dialyzer used before inclusion in the study

- Technique used: Post-dilution HDF or HD with session parameters
- Characteristics of vascular access: type (arteriovenous fistula/loop/catheter); date of implantation-creation
- Medical and surgical history, cardiovascular risk factors: diabetes (and type); hypertension; dyslipidemia; smoking habits; ischemic heart disease
- Therapeutic class of erythropoietin stimulating agents, type of administration (intravenously or subcutaneously) and initiation date.
- Iron administration and type of administration (orally, intravenously or subcutaneously) and initiation date.

### 7.5.3 Case Report Form – Clinical criteria

#### *Follow-up of the patient during the study*

During the follow-up, the following data will be collected:

- Dry weight / weight before and after dialysis / blood flow / dialysate flow / convective volume
- Possible therapeutic modifications
- Intercurrent pathology (s)
- Information on priming and restitution

### 7.5.4 Data collection

This sheet contains the various parameters to evaluate and to record and must be filled on the day of the assessments.

### 7.5.5 Anonymity

The subjects participating in the study will be coded so that their anonymity is guaranteed. They will be identified by the first three letters of their name, the first letter of their first name and the number of the center.

The Case Report Forms are identified as follows:

**CRF**     **XXX - Y**     **BIOMODAL zzz**

XXX is the first 3 letters of the patient's name.

Y is the first letter of the patient's first name.

ZZZ are the first 3 letters of the name of the center

The Investigator will assign himself the identifier (XXX-Y) of the CRF of each of his patients, identifying that he will have to fill in the sheet "Inclusion". There will be one file per patient; the identification of the CRF will remain the same for the duration of the study.

## 7.6 Associated Drugs

Any therapeutic modification will be informed.

# 8 DATA TO COLLECT AND ANALYSIS TO PERFORM

|                                                | Dialyzer A
week 1 | Dialyzer B
week 2 | Dialyzer C
week 3 | Dialyzer D
week 4 |
|------------------------------------------------|----------------------|----------------------|----------------------|----------------------|
| Parameters of the session               |                      |                      |                      |                      |
| Dry weight                                     | x                    | x                    | x                    | x                    |
| Weight before dialysis                         | x                    | x                    | x                    | x                    |
| Weight after dialysis                          | x                    | x                    | x                    | x                    |
| Duration of the session                        | x                    | x                    | x                    | x                    |
| Blood flow                                     | x                    | x                    | x                    | x                    |
| Dialysate flow                                 | x                    | x                    | x                    | x                    |
| Convective volume                              | x                    | x                    | x                    | x                    |
| KT/V                                           | x                    | x                    | x                    | x                    |
| Quality of priming                             | x                    | x                    | x                    | x                    |
| Quality of restitution                         | x                    | x                    | x                    | x                    |
| Routine biological parameters           |                      |                      |                      |                      |
| Hemoglobin pre-dialysis                        | x                    | x                    | x                    | x                    |
| Hematocrit pre-dialysis                        | x                    | x                    | x                    | x                    |
| Platelets pre-dialysis                         | x                    | x                    | x                    | x                    |
| Leukocytes pre-dialysis                        | x                    | x                    | x                    | x                    |
| Urea pre- and post-dialysis                    | x                    | x                    | x                    | x                    |
| Creatinine pre- and post-dialysis              | x                    | x                    | x                    | x                    |
| Phosphates pre- and post-dialysis              | x                    | x                    | x                    | x                    |
| Specific biological parameters          |                      |                      |                      |                      |
| Inflammation & nutrition            |                      |                      |                      |                      |
| Albumin pre-dialysis                           | x                    | x                    | x                    | x                    |
| Transthyretin pre-dialysis                     | x                    | x                    | x                    | x                    |
| CRP pre-dialysis                               | x                    | x                    | x                    | x                    |
| Middle molecules                        |                      |                      |                      |                      |
| $\beta$ 2 microglobulin pre- and post-dialysis | x                    | x                    | x                    | x                    |
| Myoglobin pre- and post-dialysis               | x                    | x                    | x                    | x                    |
| Beta trace pre- and post-dialysis              | x                    | x                    | x                    | x                    |
| Free light chains kappa pre- and post-dialysis | x                    | x                    | x                    | x                    |
| Myostatin pre- and post-dialysis               | x                    | x                    | x                    | x                    |
| Orosomucoid pre- and post-dialysis             | x                    | x                    | x                    | x                    |
| Markers of biocompatibility             |                      |                      |                      |                      |
| TNF- $\alpha$ pre- and post-dialysis           | x                    | x                    | x                    | x                    |
| IL-6 pre- and post-dialysis                    | x                    | x                    | x                    | x                    |

The hematological parameters being part of the monthly routine biology of dialysis patients, the dosages will be carried out locally by the laboratory of the dialysis center.

All other tubes will be centrifuged, aliquoted and frozen at -20 °C for further determination in a central laboratory (Montpellier). Albumin, transthyretin and CRP assays will also be performed in Montpellier to avoid any bias related to the assay techniques.

## 9 STATISTICAL ANALYSIS

### 9.1 Calculation of the sample size

This study has mainly a pragmatic exploratory orientation. It aims to try to detect differences in performance between dialyzers tested whose importance is clinically relevant. To do this, it was considered that, for the measured variables, a Cohen effect size of about 0.6 in two-to-two comparisons would meet this criterion of relevance. Under these conditions, in a bilateral situation and setting a 5% alpha risk and a 20% beta risk, a minimum of 32 patients is required.

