#### General remark

The design of this study involves the comparison of 4 dialyzers for a same patient over 4 weeks. Each week begins with the use of one studied dialyzer over 2 sessions, the second session serving as a reference. Then, the third session of the week is performed with the usual dialyzer. On this basis, the participating nephrologists have considered that any risk of persistent effect (carry-over) could be excluded and that the duration of the study was short enough to rule out a period effect related to a change in the subject's clinical status (no effect period). In addition, a randomization of the Latin square type was not considered possible for practical organization reasons at each center level.

As a result, a random order of dialyzer use was decided once (random switching of 4 elements) and this order will be applied for all patients of a same center: all patients in a given center will follow the scheme allocated to this center.

The sequence of dialyzers use will be randomly assigned: per center, device  $\times$  week allocation scheme will be generated by random permutation of a block of 4 (computer generation).

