### 9.2 Principle of the analyzes

The included population will be described in terms of demographic and medical inclusion data.

Two populations of analysis are planned: the global population including all the patients with at least one dialyzer tested and the per-protocol population (PP) including all the subjects having tested the 4 dialyzers.

The main analyzes will be conducted on the PP population and additional sensitivity analyzes on the overall population.

The main analyzes will use a univariate generalized linear model integrating the variable tested as a dependent variable and the standard hemodialysis factor (2 levels: conventional HD or HDF), the dialyzer factor (4 levels) and the center factor (4 levels) as fixed factors. A full factorial model will be applied. Two-to-two comparisons will then be conducted by adjusting the alpha risk according to the Bonferonni method.

All analyses will be carried out with Statistical Package for Social Sciences version 18.0 (IBM Inc, USA).

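### Section 9.1's minimum of 32 patients does not follow from its stated inputs, and its 5% alpha is not the Bonferroni-adjusted alpha that section 9.2 plans for the pairwise comparisons

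*Protocol*

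**What the plan says.** Section 9.1 of the protocol gives the whole sample-size argument in a few lines. It describes the study as mainly exploratory, sets the relevant difference by saying that "a Cohen effect size of about 0.6 in two-to-two comparisons would meet this criterion of relevance", and concludes that "in a bilateral situation and setting a 5% alpha risk and a 20% beta risk, a minimum of 32 patients is required". It names no test, no SD to which the effect size refers, no within-patient correlation, no allowance for drop-out and no multiplicity adjustment.

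The general remark that follows makes the design within-patient: "The design of this study involves the comparison of 4 dialyzers for a same patient over 4 weeks".

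Section 9.2 plans a linear model with modality, "the dialyzer factor (4 levels) and the center factor (4 levels) as fixed factors". No patient term is listed. It then states: "Two-to-two comparisons will then be conducted by adjusting the alpha risk according to the Bonferonni method". The main analysis is restricted to patients who tested all four dialyzers. The project summary plans 32 patients in total, the same number that section 9.1 calls the minimum.

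**The concern.** Two things do not fit. First, 32 should be reproducible from an effect size, an alpha, a power and a test. The first three are printed, and neither usual choice of test gives 32. Second, sections 9.1 and 9.2 use different significance levels for the same pairwise comparisons. Power computed at 5% does not describe tests that will be judged at 5% divided by the number of pairs.

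At stake is the only power statement in the protocol. A reader will use it to judge how much weight an inconclusive dialyzer comparison can bear. As written, it cannot be traced to its inputs and does not describe the planned tests.

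**Working it through.** **Inputs.** Effect size d = 0.6, two-sided alpha 0.05 and power 0.80 (section 9.1); stated N = 32 (section 9.1); four dialyzers per patient (general remark); Bonferroni for pairwise comparisons (section 9.2). Four dialyzers give 4×3/2 = 6 pairs, so the adjusted alpha is 0.05/6 = 0.00833.

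**Step 1: try to reproduce 32 from the stated inputs.**
- Paired, normal approximation: n = ((1.960 + 0.842)/0.6)² = 21.8, so 22. The exact paired t test (noncentral t) needs 24 (power 80.4%; 23 patients give 78.5%).
- Unpaired, normal approximation: n per group = 2×21.8 = 43.6, so 44. The exact t test needs 45 per group.
- One-sided paired: 18 (normal) or 19 (t).
- Reading *about 0.6* as 0.55 to 0.65: 28 down to 21 patients (paired t).

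None of these is 32. It appears only if an input is changed or added: Bonferroni over 3 comparisons (paired t, 80.0%); 90% power (paired t); 25% drop-out on 24 (24/0.75 = 32); d of 0.50 (normal) or 0.52 (t); or, approximately, d on the across-patient SD with a correlation of about 0.31. Section 9.1 states none of these.

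**Step 2: power of 32 completers, with 0.6 on the SD of within-patient differences.** The noncentrality is 0.6×√32 = 3.394.

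| Calculation | Alpha 0.05 | Alpha 0.05/6 |
|---|---|---|
| Paired t, 31 df | 90.8% | 71.4% |
| Repeated measures, pooled error, (32−1)×(4−1) = 93 df | 91.9% | 75.6% |
| Normal approximation | 92.4% | Φ(3.394 − 2.638) = 77.5% |

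At 0.05/6, 80% power needs 38 patients by paired t (37 give 79.8%) or 34 by the normal approximation. With fewer completers, paired t at 0.05/6 gives 67.4% for 30 and 63.0% for 28.

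**Step 3: the model as listed, without a patient term.** Take 0.6 on the across-patient SD, 32 observations per dialyzer, and 128 observations less 16 center-by-dialyzer cells = 112 error df. The noncentrality is 0.6×√(32/2) = 2.4. Power is 66% at 5% and 39% at 0.05/6. This 0.6 is on a different scale from step 2, so the two sets of figures are alternatives and do not add up.

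**Step 4: 0.6 on the across-patient SD, analysis paired.** The effect on the difference scale is 0.6/√(2(1−ρ)), where ρ is the correlation between dialyzers in the same patient. The protocol gives no ρ, so this is a range of assumptions (paired t, 32 completers, alpha 0.05/6):

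| ρ | Effect on difference scale | Power |
|---|---|---|
| 0.3 | 0.507 | 53% |
| 0.5 | 0.600 | 71% |
| 0.58 | 0.655 | 80% |
| 0.6 | 0.671 | 83% |
| 0.7 | 0.775 | 93% |

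**Step 5: difference detectable with 80% power at 0.05/6.** Solving the step 2 calculation for the effect:
- 32 completers: 0.63 (pooled error) to 0.65 (paired t) SD of within-patient differences.
- 30 completers: 0.65 (pooled error, 29×3 = 87 df) to 0.68 (paired t).
- 28 completers: 0.67 (pooled error, 27×3 = 81 df) to 0.70 (paired t).
- 16 patients, as an assumed half of the total: about 0.9 (pooled error) to 1.0 (paired t).

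**The case against.** The best defence is that the effect size is approximate and its scale open. If 0.6 refers to the across-patient SD and the analysis is paired, 32 patients do reach 80% after Bonferroni once the correlation is about 0.58, which may well be so. A reader might therefore infer too much from a flat statement that the trial misses 80% power; the protocol does not settle that. What stands is that the protocol supplies neither the scale nor the correlation, so 80% cannot be derived from it.

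The overall gap is also modest: a detectable difference of 0.63 to 0.65 is not far from about 0.6. At an unadjusted 5% with pairing, 32 is more than enough (91%). The shortfall comes from the Bonferroni step or from leaving out the patient term, and the latter is really a separate defect of the model. For the same reason, a reader might say that a single exit breaks the power claim. At the stated alpha and with 0.6 on the difference scale it does not, because 24 would do.

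A reader might also infer that section 9.1 fails within HD or within HDF. It makes no power claim by modality, and the protocol does not state 16 patients per modality; an equal split is an assumption. Nor does the protocol say that non-significant differences will be taken as equivalence.

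The exploratory label softens the consequence. It does not make a specific alpha, beta and minimum N agree with each other.

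**Conclusion.** The point holds in a limited form. The figure of 32 is not reproducible from the inputs printed beside it (24 paired, 45 per group unpaired), and it is set at an alpha that section 9.2 does not use for the pairwise tests. This is an inconsistency between two stated parts of the protocol, so it is not something that a statistical analysis plan could supply later.

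The size depends on an unstated choice. Power is 71% to 76% with 32 completers if 0.6 is on the within-patient difference scale, about 39% under the model as listed with 0.6 on the across-patient SD, and 80% or more only under a paired analysis with an across-patient d and a correlation of at least about 0.58. All these figures assume Bonferroni over all six pairs. The point should be fixed, but it does not call the design or the number of patients into question.

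**What to change.** Keep 32 patients and restate section 9.1. Name the test, state that the effect size is on the SD of within-patient differences, use two-sided alpha 0.05/6 for six pairwise comparisons, and derive the figure from a model that accounts for patient. Suggested content: with 32 completers the study has 80% power for a difference of about 0.63 (repeated-measures model with pooled error) to 0.65 (paired t) SD of within-patient differences; keep the one figure that matches the final model. Add the same figure for the expected number of completers. The restated figure is valid only if the section 9.2 model includes patient, so the two sections should be changed together.

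Optionally, because the results are meant to guide choice by modality, add that with about 16 patients per modality (labelled as an assumption) the detectable difference is about 0.9 to 1.0.

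The cost to section 9.1 is wording only and a slightly less favourable power statement. No extra patients are needed.
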